## Abstract

**Background:**

Chronic pain and access to care are identified as critical needs of the Veterans Health Administration. Music imagery and music listening interventions have shown promise as effective nonpharmacological options for pain management. However, most studies have focused on acute pain, passive music experiences, and in-person delivery.

**Objective:**

In this study, we aimed to examine the feasibility and acceptability of 2 music interventions delivered through telehealth for chronic musculoskeletal pain, trial design, and theoretical model before conducting a fully powered efficacy or comparative effectiveness trial.

**Methods:**

FAMILIA (Feasibility and Acceptability of Music Imagery and Listening Interventions for Analgesia) is a 3-arm, parallel group, pilot trial. A total of 60 veterans will be randomized to one of the three conditions: music imagery, music listening, or usual care. Aim 1 is to test the feasibility and acceptability of a multicomponent, interactive music imagery intervention (8-weekly, individual sessions) and a single-component, minimally interactive music learning intervention (independent music listening). Feasibility metrics related to recruitment, retention, engagement, and completion of the treatment protocol and questionnaires will be assessed. Up to 20 qualitative interviews will be conducted to assess veteran experiences with both interventions, including perceived benefits, acceptability, barriers, and facilitators. Interview transcripts will be coded and analyzed for emergent themes. Aim 2 is to explore the effects of music imagery and music listening versus usual care on pain and associated patient-centered outcomes. These outcomes and potential mediators will be explored through changes from baseline to follow-up assessments at 1, 3, and 4 months. Descriptive statistics will be used to describe outcomes; this pilot study is not powered to detect differences in outcomes.

**Results:**

Recruitment for FAMILIA began in March 2022, and as of July 2022, 16 participants have been enrolled. We anticipate that enrollment will be completed by May 2023. We expect that music imagery and music listening will prove acceptable to veterans and that feasibility benchmarks will be reached. We hypothesize that music imagery and music listening will be more effective than usual care on pain and related outcomes.

**Conclusions:**

FAMILIA addresses four limitations in music intervention research for chronic pain: limited studies in veterans, evaluation of a multicomponent music intervention, methodological rigor, and internet-based delivery. Findings from FAMILIA will inform a fully powered trial to identify putative mechanisms and test efficacy.

**Trial Registration:**

ClinicalTrials.gov NCT05426941; https://tinyurl.com/3jdhx28u

**International Registered Report Identifier (IRRID):**

DERR1-10.2196/38788

## Introduction

### Chronic Pain

Chronic pain, a persistent problem for United States veterans, has a reported prevalence as high as 65.5% in the veteran population and is associated with limitations in mobility and daily activities, dependence on opioids, anxiety and depression, and poor perceived health [1,2]. Chronic pain is often inadequately treated with analgesics alone and results in substantial disability, reduced health-related quality of life, and increased health care use and costs. Musculoskeletal pain accounts for more than half of all patients with pain disorders presenting for clinical care and analgesic treatment is insufficient for many patients [3,4]. To improve pain-related outcomes, the Department of Veterans Affairs (VA) recommends an integrative approach to pain management, including nonpharmacological interventions [5,6].

### Music Therapy and Pain

Music therapy interventions target biopsychosocial outcomes and show promise as nonpharmacological options for pain. Music therapists use active (music making) and receptive (music listening) interventions to support pain management; however, much of the music and chronic illness literature comprises studies that use receptive interventions [7,8]. Studies of music listening interventions have demonstrated statistically significant reductions in self-reported pain, emotional distress, and opioid use, but the findings are inconsistent and although there are a few studies that address patients with chronic pain, the focus has been primarily on acute pain [9-13]. A majority of these studies evaluated recorded music listening programs, with inconsistent findings likely because of an absence of theoretical frameworks to guide music selection and tailored delivery, and educational components to encourage independent use of music. Music listening interventions often involve minimal interaction with a music therapist, and are primarily designed to be patient self-directed, empowering patients to use music whenever needed. However, some patients with complex pain and psychological comorbidities may need a more intensive and interactive music therapy intervention that includes ongoing support, symptom monitoring, and additional treatment components, such as imagery and verbal processing, to potentially enhance the therapeutic effects of music listening.

Compared with recorded listening programs, therapist-led music therapy interventions involve more interactive approaches to music listening that provide education about the therapeutic potential of music and often integrate additional treatment components (eg, lyric discussion, drawing or journaling) to address additional biopsychosocial factors that contribute to chronic pain [14,15]. Music imagery, a receptive music therapy intervention that combines music listening, imagery, and verbal processing, has been used to address a variety of patient needs (eg, symptoms related to posttraumatic stress disorder [PTSD], cancer, mood disorders, and chronic pain [16-19]). In pilot studies with nonpain populations (eg, PTSD, health care providers), participants found that music imagery enhanced their coping skills and ability to self-regulate [16,17]. Both music listening and music imagery have shown benefits for patients with fibromyalgia and other chronic pain illnesses, including improved well-being and decreased pain, anxiety, and depression [20-22]. Taken as a whole, the music therapy literature suggests that music listening and music imagery may improve pain outcomes, but gaps in the literature include inadequate evaluations among patients with chronic pain, theoretically grounded interventions, and lack of methodological rigor.

### Telehealth Delivery

Although VA recommends using nonpharmacological interventions for chronic pain, there are significant barriers that limit access to creative arts interventions, including music therapy (eg, rural and homebound veterans [23]). Virtual delivery of health care can improve access, especially for the older adults, the mobility-impaired, and those living in rural areas or those with transportation barriers [24,25]. Case studies of virtually delivered music therapy have described veterans’ endorsement of telehealth sessions and patient-reported benefits [26]. Although these studies provide compelling preliminary data, more research is needed to develop and test specific music interventions for chronic pain that can be delivered through telehealth. In this context, we will evaluate 2 music interventions (music listening and music imagery) for veterans with chronic musculoskeletal pain.

### Study Innovation

The FAMILIA (Feasibility and Acceptability of Music Imagery and Listening Interventions for Analgesia) study addresses four limitations in music intervention research for chronic pain: few studies in veterans, evaluation of multicomponent music interventions, methodological rigor, and virtual delivery. Most previous studies described a passive, one-session, single-component music listening experience for patients with acute pain [9-13]. In contrast, the FAMILIA study will evaluate 2 music interventions in veterans. Compared with music listening, less is known about multicomponent music interventions, which we hypothesize are more robust in reducing pain owing to greater treatment intensity and more frequent interactions with a music therapist. The FAMILIA study will assess outcomes (feasibility, acceptability, pain, and associated outcomes) of a single-component, minimally interactive intervention (music listening) and a multicomponent, interactive intervention (music imagery).

Systematic reviews of music interventions for pain cite a lack of methodological rigor because of poorly described interventions, a lack of theoretical foundation, and no reporting of adverse events [27,28]. The FAMILIA study will address these methodological concerns in several ways. First, we will adhere to reporting guidelines for music-based interventions developed by Robb et al [29]. Second, we will use a theoretically based conceptual framework (Figure 1) to explore the hypothesized mechanism of action and outcomes. Third, we will systematically monitor for specific potential adverse events in both interventions.

**Figure 1 figure1:**
[figure not shown]
Study conceptual framework. MI: music imagery; ML: music listening; PTSD: posttraumatic stress disorder.

FAMILIA addresses important knowledge gaps regarding virtual delivery of music therapy interventions. The COVID-19 pandemic has rapidly accelerated the widespread use of telehealth services for multiple chronic conditions, including chronic pain, but there are few published studies to guide virtual delivery of music therapy. We recently conducted the first enterprise-wide survey examining current practices in telehealth delivery by VA creative arts therapists. Initial results indicated that 76% of creative arts therapists have delivered virtual sessions, with 74% delivering >50 sessions in the past year [30]. Telehealth provides greater access, convenience, continuity of care, and support for veterans [31,32]. Early adopters of telehealth music therapy have provided general instructive examples, but there is a need for rigorous research of music interventions delivered virtually to determine their feasibility, acceptability, and efficacy [23,26,33]. We expect that our study will inform evidence-based practice and help expand access to music interventions for chronic pain.

### Rationale and Specific Aims

The objective of this randomized controlled trial (RCT) is to examine feasibility and acceptability of the interventions, trial design, and theoretical model before conducting a fully powered efficacy or comparative effectiveness trial. Findings from FAMILIA will be used to refine the interventions and theoretical model, allowing for a comprehensive analysis of proposed mediators and outcomes in a subsequent trial. The 2 specific aims and the related key questions are shown in Textbox 1.

Study aims and key questions.
**Aims and Questions**
Study aim 1: test the feasibility and acceptability of a multicomponent, interactive music imagery intervention and a single-component, minimally interactive music listening intervention.What percentage of veterans consent to study participation, attend intervention sessions, and complete the treatment protocol and scheduled outcome assessments?What are veteran experiences with both interventions?What aspects of the interventions do veterans perceive to be most or least helpful and most or least liked?What are barriers and facilitators to study participation?How did the music interventions compare to other chronic pain treatments already tried?Study aim 2: explore the effects of both music interventions (music imagery and music listening) vs usual care on pain and associated patient-centered outcomes.What are the changes from baseline to follow-up assessments (1, 3, and 4 months) on pain and associated patient-centered outcomes?What are the changes in proximal and distal mediators, and do they vary based on group assignment?What proportion of veterans achieve a clinically meaningful change in pain intensity and pain interference?

**Figure 2 figure2:**
[figure not shown]
Flowchart of study design.

### Sample Size and Randomization

#### Recruitment

The study population will include veterans receiving care through the Richard L Roudebush VA Medical Center, Indianapolis, Indiana, United States. Inclusion criteria are veterans with chronic musculoskeletal pain of at least moderate severity (graded by ≥5 on a 0-10 scale); access to a PC, tablet, or smartphone; and ability to pass a technology screening assessment. Veterans with serious or unstable medical or psychiatric illness, housing insecurity that would prevent study participation, or suicidal ideation with current intent are excluded from participation. Veterans with hearing or cognitive impairment are also excluded because of possible interference with music listening or abstract thinking needed for music imagery work.

Veterans will be recruited from primary and specialty care clinics. Study enrollment and intervention activities will primarily be delivered virtually through Microsoft Teams, which is a VA-approved audio and video platform. Participants will be provided the options of reviewing informed consent, completing their baseline assessment, and attending their initial music imagery or music listening session in person to build rapport and identify any technology concerns. Participation and refusal rates will be tracked throughout enrollment and reported in aggregate by study group.

#### Participant Recruitment Strategies

Recruitment strategies mirror those that have been successful in multiple previous pain trials [35-38]. Primary care physicians will be informed of study details and asked to refer patients they feel could potentially participate in the study. Potential participants will be identified by querying the VA’s electronic medical record system to create a master list of veterans with the International Classification of Diseases 9th and 10th editions (ICD 9/10) codes for chronic musculoskeletal pain (ie, low back pain, neck pain or cervicalgia, fibromyalgia, and osteoarthritis). An invitation letter will be mailed to qualifying veterans to describe the study. Potential participants will be contacted by phone after the letter is mailed to assess eligibility and determine their interest in participating. Clinical staff may refer veterans who have not received a letter to the research team, and self-referral is possible by patients responding to a study brochure or advertisement displayed in primary care, orthopedic, rheumatology, pain, and rehabilitation clinics. The research team will determine eligibility by applying the inclusion and exclusion criteria to potential participants during an eligibility evaluation.

### Interventions

#### Music Imagery Group

Up to 30 participants will be randomized to receive 8 weekly music imagery sessions over 8 to 12 weeks. Allotted time will be up to 12 weeks for treatment to allow for rescheduling if needed. Each session will last approximately 45 minutes. music imagery is derived from Guided Imagery and Music, 1 of the 5 international models of music therapy practice and the most well-known receptive music therapy model [39]. The intervention uses the participant’s relationship to music to connect and enhance inner resources and provide a music resource for self-care [40]. Inner resources such as creativity, courage, and serenity connect an individual to their resiliency in the face of conflict, or to overcome some adversity. Resilience is the ability to maintain positive emotional functioning despite physical or psychological challenges [41]. An inner resource may be a visual image of a nurturing figure, the feeling of calming music, or colors that represent strength or a sense of peace. The primary aim in music imagery for chronic pain management is to address participants’ relationship to pain, their ability to interact adaptively with chronic pain, and to use supportive and accessible tools (eg, music to self-regulate through relaxation, distraction, and increased connection to inner resources) to manage pain and related psychological symptoms (eg, depression and anxiety) more effectively.

Each music imagery session will be delivered by a board-certified music therapist with specialized training in music imagery. Participants will receive individual therapist-directed sessions. The sessions include 4 steps as illustrated in Figure 3. There is a strong educational component to music imagery, partly met through weekly homework, during which participants are encouraged to *play* with the music and imagery used during the therapist-led session. In this context, *play* refers to the continued engagement with the creative process through repeated listening of music coupled with other modalities (eg, drawing, creative writing, and dancing). The music therapist and veteran identify specific ways to engage with music and imagery between sessions.

**Figure 3 figure3:**
[figure not shown]
Music imagery intervention steps. MI: music imagery.

#### Music Listening Group

In the music listening arm, a music therapist will meet with the veteran once to identify musical tastes, preferences, and activities; musical memories and social influences; and relationships between music, health, and quality of life [42]. From this meeting, an electronic playlist will be compiled for the veteran to listen to during the 12-week treatment period. The veteran will be asked to maintain a music listening log, including how long they listen, what they listen to, and any reactions to the music (eg, benefits and triggers). Music listening time will not be prescribed, but participants will be encouraged to keep track of their listening to music during the week. Our rationale for including the music listening intervention is to explore whether there is a clinically meaningful change in measures and perceived benefits from a less interactive, less intensive music intervention.

A member of the research team will check in with music listening participants (weekly for the first 3 weeks following their initial session, then biweekly following the 1-month assessment [approximately 7 check-ins in total]) to monitor safety, adherence (ie, time listening to music), and identify other issues.

#### Control Group: Usual Care

Participants in the usual care group (as is the case for the music imagery and music listening groups) may receive analgesics and nonpharmacological treatments (eg, physical therapy) for chronic musculoskeletal pain. During the study, we will systematically document participants’ receipt of usual care in all study arms, including medications, physical therapy, and clinic visits that can help pain (eg, pain specialist, psychologist, and acupuncture). A usual care arm allows us to estimate retention rates of not receiving any active treatment in the trial, informing the choice of a control condition for the planned adequately powered RCT to follow.

### Safety and Treatment Fidelity

Listening to music can at times bring up strong emotions, which can increase stress. The potential of this risk is minimal because of the supportive structure of the interventions and the overall study. The therapists are trained to help participants manage any strong emotions that emerge and, if needed, will refer participants for additional psychosocial support.

At each follow-up assessment (1 month, 3 months, and 4 months), a member of the research team will systematically check for participant intercurrent illness, adverse events, and serious adverse events. At all assessments, including baseline, a member of the research team will screen for suicidal ideation guided by a 3-step algorithm consisting of the following: (1) item 9 suicide question of the Patient Health Questionnaire-9 (PHQ-9), (2) the Columbia Suicide Severity Rating Scale Screener if item 9 of PHQ-9 is positive, and (3) Comprehensive Suicide Risk Evaluation for moderate to high risk of suicide based on the Columbia Suicide Severity Rating Scale Screener [43-45].

To ensure intervention fidelity and minimize experimental drift, we will use the following strategies: (1) standardized intervention protocols, study manuals, and training; (2) self-monitoring of intervention sessions recorded in field notes with debriefings across music therapists; (3) quality assurance checklists to track protocol deviations; and (4) therapist field notes documenting session duration and frequency (dose).

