#### Aim 1 Outcomes

Feasibility metrics include recruitment, retention, completion in allotted time (eg, 12 weeks for the music imagery group), and completion of assessments. The goal is to recruit and enroll 60 veterans into the pilot trial and to complete a median of 80% of all study visits. Those who miss visits will be called upon to ask about barriers to attendance. Individuals who dropped out of the study will be asked what could have been done to improve their participation. music imagery sessions will occur weekly on a fixed schedule while allowing some flexibility in scheduling for the participant’s convenience. The proportion of music imagery participants who complete all sessions within the treatment period will be measured. On the basis of the previous trials, the expected completed outcome assessments rate is 85%.

Acceptability of randomization to study groups will be tracked. Treatment credibility will be assessed for each music intervention and veterans’ treatment satisfaction, experience of the interventions, benefits, and barriers or facilitators to study participation will be gathered through qualitative interviews at the end of the treatment period. Safety of the music interventions will be assessed by tracking exacerbations of pain, depression, anxiety, and any adverse events.

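### Safety is asked about at roughly 10 contacts in music listening but 3 in usual care, so setting all recorded events side by side by arm could mistake frequency of asking for harm

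*Protocol article*

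**What the plan says.** The statements that fix the safety schedule are spread over several sections of the Protocol article.

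- **All arms** (Safety and Treatment Fidelity): "At each follow-up assessment (1 month, 3 months, and 4 months), a member of the research team will systematically check for participant intercurrent illness". The full list is "intercurrent illness, adverse events, and serious adverse events". No arm is excluded.
- **Music listening** (Music Listening Group): weekly contacts for 3 weeks, "then biweekly following the 1-month assessment [approximately 7 check-ins in total", with the stated purpose "to monitor safety, adherence (ie, time listening to music), and identify other issues".
- **Music imagery** (Music Imagery Group): "Up to 30 participants will be randomized to receive 8 weekly music imagery sessions over 8 to 12 weeks". Data Collection and Measures, Overview, adds brief feedback after each session and a before-and-after visual analog scale for symptoms such as pain and anxiety. Neither is described as an adverse event query.
- **Usual care** (Control Group: Usual Care): no additional safety contact is described.
- **Safety outcome** (Aim 1 Outcomes): "Safety of the music interventions will be assessed by tracking exacerbations of pain, depression, anxiety, and any adverse events". It does not say from which contacts the events are counted.
- **Intention** (Study Innovation): specific potential adverse events are to be monitored systematically in both interventions. The contacts are not named, and usual care is not mentioned.

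Table 1 schedules the pain rating scale, PHQ-9 and GAD-7 at baseline and at 1, 3 and 4 months, with no arm restriction stated.

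**The concern.** The number of adverse events recorded depends on how many occur and on how often people are asked. Here the second factor differs by arm by design. Pain, depression and anxiety can worsen without any treatment effect, and participants enter with pain of at least 5 out of 10. An exacerbation count in a music arm is therefore hard to attribute to the music without a usual care count obtained in the same way.

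The article presents adverse event monitoring as one of its remedies for weaknesses in earlier music trials, and its findings are meant to shape the next trial. With about 15 participants in each of the music listening and usual care arms, a few events found only because someone telephoned could look like a safety signal. The two music arms also differ from each other: one has explicit safety check-ins, the other has therapist sessions.

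**Working it through.** **1. Reproduce the plan's own figure.** Music listening runs for 12 weeks ("listen to during the 12-week treatment period"). Weekly check-ins fall at weeks 1, 2 and 3. Biweekly ones after a 1-month assessment at week 4 fall at weeks 6, 8, 10 and 12. That gives 3 + 4 = 7, which matches the article's approximate figure.

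**2. Count contacts by arm.**

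| Arm | Common checks | Other contacts with a stated safety purpose | Total | Other contacts, no adverse event query stated |
|---|---|---|---|---|
| Music listening | 3 | about 7 | about 10 | initial session |
| Music imagery | 3 | none stated | 3 | 8 sessions |
| Usual care | 3 | 0 | 3 | none described |

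Music listening to usual care: 10 / 3 = 3.3. For music imagery, 3 + 8 = 11 counts contacts, not safety queries.

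**3. What unequal asking could do to the event count.** The article gives no recall period, so one must be assumed. Assumptions: common assessments at weeks 4, 13 and 17; the same constant event rate in every arm; an event is recorded only if a contact follows within the recall window. Then:

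share captured = (weeks lying within the recall window before any contact) / 17

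- *2 weeks, usual care:* 3 × 2 = 6 weeks; 6/17 = 0.35.
- *2 weeks, music listening:* gaps between contacts never exceed 2 weeks up to week 13, so 13 weeks are covered, plus weeks 15 to 17; 15/17 = 0.88. Ratio 15/6 = 2.5.
- *4 weeks, usual care:* weeks 0–4, 9–13 and 13–17; 12/17 = 0.71.
- *4 weeks, music listening:* 17/17 = 1.00. Ratio 17/12 = 1.4.
- *9 weeks:* the longest gap between common checks is 13 − 4 = 9 weeks, so every arm is fully covered. Ratio 1.0.

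| Assumed recall | Usual care | Music listening | Ratio | Music imagery, only if its sessions act as queries | Ratio |
|---|---|---|---|---|---|
| 1 week | 0.18 | 0.59 | 3.3 | 0.59 | 3.3 |
| 2 weeks | 0.35 | 0.88 | 2.5 | 0.71 | 2.0 |
| 4 weeks | 0.71 | 1.00 | 1.4 | 0.94 | 1.3 |
| 9 weeks | 1.00 | 1.00 | 1.0 | 1.00 | 1.0 |

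The music imagery columns place the sessions at weeks 1 to 8. If its sessions elicit nothing, its ratio to usual care is 1.0 throughout.

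**4. A gentler form of forgetting.** Suppose the chance of reporting halves every h weeks between the event and the next contact. The music listening to usual care ratio is then 1.7 for h = 2, 1.4 for h = 4, 1.2 for h = 8 and 1.06 for h = 26. The direction is the same and the size smaller.

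**5. In events.** Suppose, purely for illustration, 15 transient events truly occur in each arm of 15. With 2-week recall, usual care records 15 × 6/17 = 5.3 and music listening 15 × 15/17 = 13.2. With 4-week recall the figures are 15 × 12/17 = 10.6 and 15.0.

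**6. After the fix.** Counting only the 1-, 3- and 4-month checks gives 3, 3 and 3 contacts.

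**The case against.** Three stronger readings are tempting, and the article supports none of them.

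- *A reader might infer that adverse events are sought at 11 contacts in music imagery.* The article writes no such query for the 8 sessions; the feedback concerns content and delivery, and the scale measures immediate effects. Events may surface there, and worsening of pain or anxiety may be recorded there, but the documented safety checks number 3, as in usual care. This is the largest arm, about 30 of 60.
- *A reader might infer that a biased safety comparison is planned.* Aim 1 speaks of the safety of the music interventions. Data Analysis names between-group tests for antecedent, mediator and outcome variables without naming adverse events. The usual care arm is justified by retention and the choice of a future control. The problem arises only if events are set side by side by arm.
- *A reader might infer that the music arms will show more events.* If each systematic check truly covers everything since the last one, there is no excess.

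It can also be said that extra monitoring of a self-directed intervention is ordinary participant protection, that equally scheduled data already exist, and that tabulation by source belongs in a fuller document. The first two are right, and the fix relies on them. The third stands only in part. A full protocol or analysis plan, not shown, may already contain the rule, but the unequal schedule and the undivided safety outcome are both written in the article. Safety sits among the Aim 1 outcomes of a three-arm trial that also collects events in usual care, so a side-by-side table is a natural way to report it.

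**Conclusion.** The concern holds in a limited, conditional form. Contacts with a stated safety purpose number about 10 in music listening and 3 in usual care; music imagery has 3 plus 8 sessions of unspecified safety content. Nothing in the safety outcome keeps these sources apart, so pooling all recorded events by arm would mix harm with frequency of asking, chiefly for music listening.

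The distortion ranges from none (recall covering the 9-week gap) through about 1.4-fold (4 weeks) to about 2.5-fold (2 weeks). Those ratios rest on an assumed recall period, a constant event rate and nominal visit weeks. They illustrate a possible range and are not estimates for this trial. The arm-specific monitoring is not itself a fault. A counting rule is worth adding because it is nearly free and protects an Aim 1 outcome.

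**What to change.** Keep the arm-specific monitoring as it is. In Aim 1 Outcomes, add that any between-arm safety result uses only:

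1. events elicited by the identical check at 1, 3 and 4 months; and
2. exacerbations derived from the pain rating scale, PHQ-9 and GAD-7 at those same times, with one definition for all three arms.

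Ask the common check in full, covering the time since the previous assessment, even when an event has already been mentioned at a check-in or session; otherwise the music arms could be undercounted. Record on the event form the contact at which each event was reported. List events found only at check-ins or sessions separately by arm, outside the comparison.

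The cost is a sentence or two of text and one data field, with no new visit or measure. The downside is that the comparison rests on fewer events and misses short-lived ones between assessments, though all events are still reported.
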